## Abstract

**Background:**

Paratonia, a form of hypertonia, is associated with loss of mobility and with the development of contractures especially in the late stages of the dementia.

Passive movement therapy (PMT) currently is the main physiotherapeutic intervention. General doubt about the beneficial effects of this widely used therapy necessitates a randomised clinical trial (RCT) to study the efficacy of PMT on the severity of paratonia and on the improvement of daily care.

**Methods/Design:**

A RCT with a 4-week follow-up period. Patients with dementia (according to the DSM-IV-TR Criteria) and moderate to severe paratonia are included in the study after proxy consent. By means of computerised and concealed block randomisation (block-size of 4) patients are included in one of two groups. The first group receives PMT, the second group receives usual care without PMT. PMT is given according to a protocol by physical therapist three times a week for four weeks in a row. The severity of paratonia (Modified Ashworth scale), the severity of the dementia (Global Deterioration Scale), the clinical improvement (Clinical Global Impressions), the difficulty in daily care (Patient Specific Complaints) and the experienced pain in daily care of the participant (PACSLAC-D) is assessed by assessors blind to treatment allocation at baseline, after 6 and 12 treatments.

Success of the intervention is defined as a significant increase of decline on the modified Ashworth scale. The 'proportion of change' in two and four weeks time on this scale will be analysed. Also a multiple logistic regression analysis using declined/not declined criteria as dependent variable with correction for relevant confounders (e.g. stage of dementia, medication, co-morbidity) will be used.

**Discussion:**

This study is the first RCT of this size to gain further insight on the effect of passive movement therapy on the severity of paratonia.

**Trial registration:**

Current Controlled Trials ISRCTN43069940

## Background

Paratonia is one of the motor problems seen in persons with dementia and was first described by Dupré in 1910 as the inability to relax muscles in combination with a mental disorder [1]. Paratonia is hypothesized to develop centrally but to exert an effect on peripheral biomechanics. Especially in the late stages of dementia it is associated with loss of mobility and with the development of contractures [2-5]. Thus, paratonie has a negative impact on the quality of life and can result in problems with washing and dressing

The prevalence of paratonia ranges from 5% in the early stages of dementia to 100% in the advanced stages [2,5]. We found an estimated prevalence of paratonia of approximately 80% in a group of Dutch nursing home patients with dementia [6]. Passive movement therapy (PMT) is a therapeutic intervention designed to increase the passive extensibility of muscles, ligaments and collagen in order to achieve maximal joint range of motion [7,8]. A recent NIVEL report revealed that PMT is with 28.2% one of the main physiotherapeutic interventions in Dutch nursing homes, with an average duration of 30 minutes per patient per week [9]. This therapy is generally believed to be effective in patients with paratonia [10,11]. Professional workers claim that this therapy, if given shortly before washing and bathing, facilitates the care for the patients, due to improved range of motion of affected limbs. Investigations in other populations, e.g., patients with spasticity and contractures show a temporal effect or a so-called elastic deformation due to the visco-elastic properties in all tissues [7]. However, after 20 to 30 minutes, joint range of motion returns to the starting values. Plastic deformation, or a permanent effect, is only possible if the patient can actively use the gained mobility[7,8]. Furthermore, animal studies indicate that when activated muscles fibres are stretched, which is the case with PMT in paratonia, older tissues are more susceptible to injury on sarcomere level [12]. Given the fact that these frail patients, who often show signs of discomfort during the treatment, are prone to injury and are not able to actively use regained mobility PMT is controversial. Nonetheless, maybe because of a lack of alternatives, or because of pressure of concerned relatives, physicians and physiotherapist start PMT. A pilot study in 15 patients with paratonia confirmed that PMT had positive short term effects, but trend analyses of long term effects showed that after 3 weeks hypertonia increased slightly in 30% in the PMT group in comparison with 10% in the control groups, indicating a possible association with muscle fibre injuries [3]. We feel this is a relevant finding, however, the small sample size of this pilot study, and the lack of a clear operational definition of paratonia did not allow for firm conclusions concerning the efficacy of PMT.

Before designing a new trial with sufficient power we therefore initiated a Delphi procedure with known experts in the field to achieve a new consensus definition of paratonia. After four Delphi-rounds, the experts agreed on 7 criteria for operational defining paratonia (see below) [13]. Consequently these criteria have been assessed on validity and reliability in a 3-phase cross-sectional study in which this definition was tailored even further and in which we developed an assessment instrument (the Paratonia Assessment Instrument, PAI) for an instant diagnosis of paratonia, thus providing researchers an operational tool for future trials on paratonia [6].

*"Paratonia is a form of hypertonia with an involuntary variable resistance during passive movement. The nature of paratonia may change with progression of the dementing illness (e.g. active assistance (Mitgehen) is more common early in the course of degenerative dementias, whilst active resistance is more common later in the course of the disease). The degree of resistance varies depending on the speed of movement (e.g. a low resistance to slow movement and a high resistance to fast movement). Paratonia increases with progression of dementia. Furthermore, the resistance to passive movement is in any direction and there is no clasp-knife phenomenon." The resistance must be felt in either two directions in one limb or in two different limbs*.

We designed a randomized clinical trial in order to answer three research questions; first, is passive movement therapy an effective intervention on the severity of paratonia in comparison with usual care without passive movement therapy?

Second, is passive movement therapy an effective intervention for improvement of daily care? And finally, does PMT reduce pain during daily care in patients with moderate to severe paratonia.

## Methods

To answer these 3 research questions we use a randomised clinical trial with 4 weeks of follow-up.

### Patients

The study population consists of patients with dementia (according to the DSM-IV-TR Criteria) and established paratonia according to the Paratonia Assessment Instrument (PAI). The PAI is a construct of five criteria derived from the definition, representing distinct elements of the clinical manifestation of paratonia [6]. The resistance felt during passive movement due to paratonia has to be at least in one of the limbs more marked i.e. a score of 2 or more on the modified Ashworth scale. Possible participants will be identified by trained personnel of participating nursing homes. After identification of participants the researcher checks if the patient is eligible for the study and if so will contact the legal representative(s) of the patient by sending an information leaflet about the study. Patients are only included after proxy consent. Because patients are included after proxy consent we will exclude participants who indicate during the trial in any way, verbally or nonverbally, not to approve of participation. Patients with an unstable disease, as judged by the nursing home physician, such as progressive malignant cancer or other diseases with an obvious progressive negative effect on the motor function or health status are excluded as well as patients who received passive movement therapy within a period of 4 weeks prior to admission or who receive typical or a-typical antipsychotics.

### Interventions

Patients are included in one of two groups after computerised and concealed block randomisation (block size of four). The first group receives usual care with PMT, the second group receives usual care without PMT. Usual care generally consists of grooming and dressing with slow and gentle movements by trained nurses. Some of the participants wear especially designed clothing that enables the nurses to dress patients more easy while the patient is lying in bed or sitting in a wheelchair. Most participants use cushions, mostly manufactured on demand, for a stable position in bed and sit during the day time in comfortable wheelchairs.

PMT is provided in a standardized way. During the first part of passive movement the therapist moves slowly the affected limbs, with the emphasis on lowering the resistance. After this, the therapist tries to reach the end range of motion and possibly stretches the structures very lightly without causing pain. The patients are positioned comfortably supine in bed while the therapist starts PMT with the left arm moving it in flexion and extension (up and down). Subsequently PMT is performed on the right arm, left leg and finally the right leg. The duration of PMT is approximately 20 minutes per patient per session. The treatment group receives PMT, between 8 a.m. and 10 a.m., shortly before being washed and dressed by nursing staff, three times a week for four weeks in a row. In order to safeguard blinding of the assessors for treatment allocation, the control group receives a placebo treatment in the same frequency and in the same time frame. The patients of the control group are positioned comfortably supine in bed after which the therapist stays in the room for approximately 20 minutes. On every treatment day a special signboard on the participant's bedroom door indicates that research is going on advising nursing staff to delay their activities with the participant and not disturb the treatment session.

### Outcome measures

The Modified Ashworth scale is the primary outcome measure and tested with an acceptable reliability to assess the severity of paratonia (intrarater reliability; Kendall's Tb 0.62–0.80 and interrater reliability; Kendall's Tb 0.72–0.77) [14]. It is a 5 point scale ranging from 0 to 4, in which 0 = no resistance to passive movement, 1 = slight resistance during passive movement, 2 = more marked resistance to passive movement, 3 = considerable resistance to passive movement, 4 = severe resistance, passive movement is impossible. Severity of paratonia will be assessed by assessors blinded to treatment allocation at baseline one day prior to treatment start, one day after treatment 6 (after 2 weeks) and one day after treatment 12 (after 4 weeks) between 8 a.m. and 10 a.m. before washing and dressing by nursing staff.

To assess the severity of paratonia all four limbs will be passively moved in flexion and extension with the participant in a comfortable position supine in bed.

As secondary outcome measures we assess The Pain Assessment Checklist for Seniors with Limited Ability to Communicate (PACSLAC-D) [15,16], to assess a decrease of pain as a possible side effect of PMT The PACSLAC-D is an observational assessment instrument that lists 24 items divided in three categories; nonverbal facial signs (10 items), total resistance (6 items) and emotional state (8 items). This version, a reduction of the original 60 item PACSLAC scale had high levels of internal consistency for the complete scale (Cronbach's alpha range 0.82–0.86) and for all subscales (alpha range 0.72–0.82) [17].

An independent observer will assess the PACSLAC-D in both groups by a 5-minute observation of washing and dressing within an hour after the first, sixth and the twelfth treatment session. Another secondary outcome measure is the Clinical Global Impressions scale (CGI) to assess clinical change. With this CGI, especially appointed nurses, who are blinded for treatment allocation, compare the participant with all other patients with paratonia on their ward on a 7 point scale from normal to most severe and rate after 2 and 4 weeks the global improvement also on a 7 point scale from very much improved to very much worse. Finally, the modified "Patient Specific Complaint" (PSC) assessment is used, in which the nurses are asked to address the 3 most difficult items in daily care and rate these items on a visual analogue scale of 100 mm, with at the extreme ends "no trouble at all" and "impossible". The frequencies of all assessments are illustrated in Table 1.

**Table 1 T1:** Assessment schedule

**Assessment scale *(Assessed by)***	**T0**	**T1**	**T2**
**Modified Ashworth *(Assessor, blind for treatment allocation)***	One day prior to treatment start	One day after treatment 6	One day after treatment 12
**PACSLAC *(independent assessor, blind for treatment allocation)***	on the day of the first treatment	On the day of the sixth treatment	On the day of the twelfth treatment
**CGI and PSC *(Nurse, blind for treatment allocation)***	One day prior to treatment start	One day after treatment 6	One day after treatment 12
**GDS *(Nurse)***	Within a week before trial start		

At baseline we will register demographic information and relevant variables such as age, sex, use of medication, type of dementia and severity of the dementia. Severity of dementia is assessed with the Global Deterioration Scale which consists of seven stages of cognitive decline in which stage 1 = no cognitive decline, level 2 = very mild cognitive decline, level 3 = mild cognitive decline, level 4 = moderate cognitive decline, level 5 = moderately severe, level 6 = severe and level 7 = very severe cognitive decline [18]. Psychoactive medications will be classified using the Anatomical Therapeutical Chemical-classification and grouped into antipsychotics, anxiolytics, hypnotics/sedatives, antidepressants, anti-epileptics and miscellaneous (e.g. cholinesterase inhibitors) [19].

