### Analysis

All data will be analysed with SPSS 15.0. The Modified Ashworth scale, an ordinal 5-point scale, will be measured at 3 times, at baseline (T0) after 2 weeks (T1) and after 4 weeks (T2). Our premise in this study is that PMT causes an accelerated worsening of paratonia over 4 weeks time. Success of the intervention is defined as a significant (p < 0.05) difference between the proportion of change on the modified Ashworth scale in the two groups.

To determine any development or change over time of The Modified Ashworth score in the two groups the Stuart-Maxwell statistic will be used.

The difference in proportion of change between the two groups will be calculated and tested for significance [20]. However controlling for relevant confounders e.g. age, sex, severity and type of dementia is not possible with this analysis. Therefore a multiple logistic regression analysis will be performed on the dichotomised outcome measure, "declined" and "stable/improved", of the difference on T0 and T2 on The Modified Ashworth score.

Missing data will be assumed to be missing at random. The Last Observation Carried Forward method will be used in those cases with no last measurement (T2) yet with valid data from the second assessment (T1). Analyses will be carried out according to the intention to treat principle.

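### The T0 pain score (PACSLAC-D) is taken after the first treatment session, so the pain outcome has no pre-treatment value and T0 cannot serve as a baseline

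*Protocol article*

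**What the plan says.** The third research question (Background) asks: "does PMT reduce pain during daily care in patients with moderate to severe paratonia". PACSLAC-D is the instrument for it. Outcome measures gives its purpose as "to assess a decrease of pain as a possible side effect of PMT".

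The same section has an independent observer watch five minutes of "washing and dressing within an hour after the first, sixth and the twelfth treatment session". In Table 1 the PACSLAC entry in the T0 column reads "on the day of the first treatment". For the Modified Ashworth scale (MAS), the Clinical Global Impressions scale (CGI) and the Patient Specific Complaints (PSC), the T0 entry is "One day prior to treatment start". The abstract (Methods/Design) names five measures together, PACSLAC-D among them, as assessed "at baseline, after 6 and 12 treatments". No earlier, untreated PACSLAC-D observation is described.

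The Analysis section equates T0 with baseline, but only for the MAS. It gives no analysis for PACSLAC-D.

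**The concern.** By the T0 pain observation, the active arm has had a session of passive movement therapy (PMT) and the control arm has had the placebo stay in the room. T0 is then an early outcome that differs in kind between the arms. It cannot show whether the arms started with similar pain, and it cannot safely be used to gain precision.

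This matters more because the article expects an immediate effect on care. PMT is given shortly before washing and dressing (Interventions). The Background reports the claim that PMT at that moment makes care easier, and positive short-term effects in the pilot. Pain is observed in the same window. If T0 is later treated as the baseline, which its column and the abstract's label invite, that immediate effect is partly or wholly removed from the comparison.

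**Working it through.** **Inputs from the article.** Alpha 0.05, power 80%, worsening in 30% against 10%, 69 per group including 10% drop-out (Sample size). All three PACSLAC-D observations follow a session (Outcome measures).

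**The plan's own figure.** Two-sided comparison of proportions, no continuity correction:

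n = [1.96·√(2·0.2·0.8) + 0.8416·√(0.3·0.7 + 0.1·0.9)]² / 0.2² = (1.109 + 0.461)² / 0.04 ≈ 61.6, so 62; and 62/0.9 = 68.9, so 69.

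The stated size reproduces. It concerns the MAS and does not bear on the timing, but it gives 62 evaluable patients per arm for the illustration.

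**What each analysis would estimate.** Let a be the immediate effect of one session on pain in the care that follows, and c the further cumulative effect by T2. Negative means less pain. The expected difference, PMT minus control, is a at T0 and a + c at T2.

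- T2 score, unadjusted: a + c.
- Change T2 − T0: (a + c) − a = c.
- T2 adjusted for the post-session T0: (a + c) − rho·a = c + (1 − rho)·a.
- T2 adjusted for a pre-treatment value: a + c.

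**Illustration.** The article gives no SD, effect or correlation for PACSLAC-D. I assume SD 1, rho of 0.5 to 0.7 for any pair of observations, and n = 62 per arm. Power = Φ(|contrast| / (s·√(2/62)) − 1.96), with √(2/62) = 0.180. Here s = 1 for the T2 score, √(2(1 − rho)) = 1.00 to 0.77 for change, and √(1 − rho²) = 0.87 to 0.71 with adjustment. The small extra variance from a covariate that differs between arms is ignored. Ranges run from rho 0.5 to rho 0.7.

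| Assumed effect (SD) | Change from T0 | Adjusted for T0 | T2 unadjusted | Adjusted for pre-treatment value |
|---|---|---|---|---|
| a = −0.5, c = 0 | contrast 0; 5% | −0.25 to −0.15; 36% to 22% | −0.5; 80% | −0.5; 90% to 97% |
| a = −0.5, c = −0.25 | −0.25; 29% to 44% | −0.5 to −0.4; 90% to 88% | −0.75; 99% | −0.75; over 99% |
| a = 0, c = −0.5 | −0.5; 80% to 95% | −0.5; 90% to 97% | −0.5; 80% | −0.5; 90% to 97% |

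In the first cell the contrast is zero, so power equals the type I error rate.

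**Direction.** If a and c have the same sign, |c| is smaller than |a + c| and the change score is pulled towards zero. If they oppose, it is not a simple dilution. With a = −0.3 and c = +0.4, the T2 difference is +0.1 but the change contrast is +0.4, which is inflated. With a = −0.5 and c = +0.5, the T2 difference is 0 and the change contrast is +0.5. When the immediate effect is the larger of the two, the change contrast has the opposite sign to the T2 difference.

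**The case against.** The strongest reply is that the article states no analysis of PACSLAC-D from T0. Change scores and T0-to-T2 differences are specified for the MAS only, and the handling of a secondary outcome may properly sit in a document not shown. An unadjusted randomised comparison at T1 and T2 is valid on the present schedule and answers the third research question. This stands. A reader might infer that the pain comparison in this plan is biased, or has 5% power whatever the effect; the article does not support that, because it does not commit to the analysis that would cause it.

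It is also tempting to say that the bias runs towards zero. That is assured only if the immediate and cumulative effects do not oppose each other. The article's own premise allows opposition: short-term benefit in the pilot, with worsening of paratonia over weeks. Nor would the whole pain effect be lost, since whatever builds up after session 1 remains estimable.

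Two further limits apply to the evidence. Table 1 says only that T0 falls on the first treatment day; the post-session timing comes from the running text. The abstract is a loose summary: it gives the same three time points to the Global Deterioration Scale, which Table 1 schedules once. It should not be read as a deliberate statement about when pain is measured.

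What the reply does not remove is the missing pre-treatment value. No later analysis can recover it.

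**Conclusion.** The point holds as a design weakness of moderate severity. The T0 PACSLAC-D is a post-treatment observation, unlike T0 for the MAS, CGI and PSC, and the pain outcome has no pre-treatment value for balance checks or precision. That loss is certain. Under the assumed rho of 0.5 to 0.7 and a 0.5 SD effect, it is the gap between about 80% power unadjusted and about 90% to 97% with a true baseline.

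The distortion is conditional on T0 being used as a baseline. A change score then removes all of the immediate single-session effect and adjustment removes a share rho of it. If there is no immediate effect, nothing is distorted. The power figures rest on assumed values; the algebra does not.

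The rating stays at moderate because PACSLAC-D is secondary, and the primary outcome, the sample size and the success definition do not depend on it. It is not lower because PACSLAC-D is the only instrument for one of the three research questions.

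**What to change.** Move the T0 PACSLAC-D observation to washing and dressing on the day before treatment starts, alongside the T0 MAS, CGI and PSC. Keep the observations after sessions 6 and 12 as T1 and T2, and analyse them adjusted for the pre-treatment value. Amend Table 1, the Outcome measures text and the abstract to agree.

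For patients already observed on the present schedule, treat the session-1 score as a post-treatment outcome and neither subtract it nor adjust for it.

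The cost is one five-minute observation moved one day earlier, with the same observer and the same number of observations. The session-1 observation is lost unless it is kept as an additional post-treatment time point, which adds five minutes of observation per patient.

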### Sample size

The Modified Ashworth Scale is our primary outcome measure. A trend analysis of the pilot study data showed a worsening of paratonia in 30% of the group with PMT and in 10%, possibly due to natural course, of the group with usual care without PMT [3]. We consider this effect as clinical important. With an alpha of 0.05 and a power of 80% a sample size of 69 patients per group (taking into account a drop-out percentage of 10%) is needed to detect this effect.

### Analysis

All data will be analysed with SPSS 15.0. The Modified Ashworth scale, an ordinal 5-point scale, will be measured at 3 times, at baseline (T0) after 2 weeks (T1) and after 4 weeks (T2). Our premise in this study is that PMT causes an accelerated worsening of paratonia over 4 weeks time. Success of the intervention is defined as a significant (p < 0.05) difference between the proportion of change on the modified Ashworth scale in the two groups.

To determine any development or change over time of The Modified Ashworth score in the two groups the Stuart-Maxwell statistic will be used.

The difference in proportion of change between the two groups will be calculated and tested for significance [20]. However controlling for relevant confounders e.g. age, sex, severity and type of dementia is not possible with this analysis. Therefore a multiple logistic regression analysis will be performed on the dichotomised outcome measure, "declined" and "stable/improved", of the difference on T0 and T2 on The Modified Ashworth score.

Missing data will be assumed to be missing at random. The Last Observation Carried Forward method will be used in those cases with no last measurement (T2) yet with valid data from the second assessment (T1). Analyses will be carried out according to the intention to treat principle.

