### Bias

With the use of the consensus definition a homogeneous population should be guaranteed although research in the more severe cases of paratonia indicates that if the resistance in affected limbs is very high the assessor is not able to accelerate the movement and adequate differentiation with Parkinsonian (lead pipe) rigidity becomes impossible [6]. Furthermore, we did not specify the type of dementia in the inclusion criteria. At this moment we know that in the advanced stages of the disease all patients have paratonia. However, it is unclear if there are any dissimilarities in the development and severity of paratonia in different types of dementia. Therefore paratonia, diagnosed in different dementias, could react inconsistently to PMT and although we take this into account in our analysis this uncertainty could be a potential source of bias.

With this study, we hope to clarify the effect of passive movement therapy on moderate to severe paratonia and hopefully gain some scientific basis for the use of this treatment or to abandon PMT in this population. The controversy between the hypothesis of the research team that PMT is possibly harmful and the assumption of nurses and relatives that it is beneficial, necessitates a thorough organisation for keeping all assessors blind for treatment allocation. Therefore randomisation is done in a block size randomisation system with block size of four. For each participating nursing home a new sequence is calculated at the faculty of Epidemiology of the Maastricht University. The blinding of the assessors can be compromised by an incidental verbal hint of one of the participants although most of the participants are in the advanced stage of dementia and lost there capacity of speech.

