### validity

The research will be conducted in four different nursing homes, that will enhance extrapolation of study findings. However, due to the fact that at least 4 different geriatric physical therapists will perform PMT and at least two different assessors of the severity of paratonia will participate, the internal validity may become compromised. A protocollized way of performing PMT and an extensive training of all therapists and assessors involved should ensure internal validity of this study and reliability of assessed outcomes.

The results of this randomised controlled trial will be published in a scientific journal and will be used for recommendations in the guideline of geriatric physical therapy and implemented in current physical therapy practice. This guideline will be developed according to method of clinical practice guideline development of the Royal Dutch Physiotherapy Association (KNGF) [21].

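### Randomisation is separate for each nursing home, but the success test ignores home, and neither home nor the T0 Ashworth score is named for the logistic model

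*Protocol article*

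**What the plan says.** **Randomisation.** The Interventions section states: "Patients are included in one of two groups after computerised and concealed block randomisation (block size of four"). The Bias section adds: "For each participating nursing home a new sequence is calculated". The validity section gives four homes, says that "at least 4 different geriatric physical therapists will perform PMT", and expects at least two assessors of severity. Home is therefore a stratification factor by design.

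**Success test.** The Analysis section defines success as a significant difference (p < 0.05) between the groups in the proportion of change on the Modified Ashworth scale. It describes a two-group comparison and mentions no strata.

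**Adjusted analysis.** The Analysis section says of the test of proportions that "controlling for relevant confounders e.g. age, sex, severity and type of dementia is not possible with this analysis". It therefore adds a multiple logistic regression of declined v stable or improved, from T0 to T2. The abstract describes the same regression with "correction for relevant confounders (e.g. stage of dementia, medication, co-morbidity"). Both lists are given as examples. Neither names nursing home or T0 Ashworth.

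**Scale and entry.** The scale runs from 0 to 4 (Outcome measures), and a patient needs a score of 2 or more in at least one limb (Patients).

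**The concern.** Blocking within home keeps the arms balanced in each home, so differences between homes largely cancel out of the treatment comparison. A test that ignores home still counts those differences as noise. Its standard error is then too large, and part of what the blocking bought is lost. Homes may well differ here: therapists and assessors may differ between them, and the validity section itself raises this as a threat.

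The T0 Ashworth score matters for a different reason. The outcome is a rise from T0 on a scale that stops at 4, so T0 partly determines who can have the event at all. It is measured in every patient and is the most direct prognostic variable available.

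The stated reason for leaving covariates out of the proportion test also goes too far. It may hold for age or a list of several variables. It does not hold for one four-level factor, which a Mantel-Haenszel analysis handles directly.

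At stake are a few points of power, and an adjusted model that uses the design factor and the baseline rather than weaker covariates.

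**Working it through.** **1. The plan's own figure.** Inputs from Sample size: 30% v 10% worsening, alpha 0.05, power 80%, drop-out 10%. Sidedness is not stated; two-sided, pooled, without continuity correction reproduces the figure.

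n = [1.96 × √(2 × 0.20 × 0.80) + 0.84 × √(0.30 × 0.70 + 0.10 × 0.90)]² / 0.20² = 61.6, so 62 per group; 62 / 0.90 = 68.9, so 69. The sample size is correct.

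**2. Expected declines.** 62 × 0.30 + 62 × 0.10 = 18.6 + 6.2 = 24.8, with a chance range of about 17 to 33. If all 69 per group are evaluable, the figure is 69 × 0.40 = 27.6.

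**3. Unstratified v home-stratified test.** This is a simulation with 40,000 replicates, four homes and 16 patients per arm in each (64 per arm, close to the planned 62). The 10% and 30% are held as overall rates, because that is what Sample size gives. Type I error is taken at a common rate of 20%. The documents give no between-home spread, so a range is shown. The stratified test is CMH without continuity correction.

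| Home log-odds SD (assumed) | Power, unstratified | Power, CMH | Gain (points) | Type I error, unstratified |
|---|---|---|---|---|
| 0 | 82.5% | 82.7% | 0.2 | 4.9% |
| 0.5 | 82.8% | 83.6% | 0.8 | 4.5% |
| 1.0 | 82.8% | 85.0% | 2.2 | 3.9% |
| 1.5 | 82.4% | 86.6% | 4.2 | 3.2% |

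The type I error of CMH stays at 4.8% to 5.0% throughout. With a continuity correction, CMH falls to 76% to 80% power, below the plain test, so the wording must exclude it.

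**4. Home and T0 Ashworth in the logistic model.** This is a separate simulation of 3,000 trials with 124 patients. The covariate distributions are assumed, with home SD 0.7 and a T0 slope of −0.7 on the logit scale. Power was 81.8% unadjusted, 80.5% with the Analysis section's list, and 84.5% with home and T0 Ashworth. Type I error was 5.2%, 5.8% and 6.0%, so a small part of the 84.5 − 81.8 = 2.7 points reflects a slightly liberal test. Implausibly large or separated coefficients occurred in 2.5% of the home-plus-T0 fits.

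**5. Parameters against events.** Treatment (1) + home (3) + T0 Ashworth (1) = 5, or 24.8 / 5 = 5.0 events per parameter. Treatment with the Analysis section's list, assuming three dementia types and linear severity, has 6 parameters, or 24.8 / 6 = 4.1. Adding home and T0 to that list gives 10, or 24.8 / 10 = 2.5.

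**The case against.** The strongest reply is that nothing has been excluded. Both covariate lists are open examples, and an article may leave the full model to a plan that is not shown. That stands for the regression, and the point is worded accordingly: home and T0 Ashworth are not named. It does not dispose of the success test, which the article describes as a two-group comparison.

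A second reply is that validity is untouched, the home SDs have no source, and an SD of 1.5 is extreme: around a 10% rate it implies homes ranging from 0.6% to 68% decline. This too stands, and it is why the gain should be read as about 1 to 4 points, with the lower end as plausible as the upper. A much larger loss appears only if 10% and 30% are treated as typical-home rates, which changes the overall rates that Sample size states.

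A third reply is that five parameters on 25 events is also sparse. That is correct, and it is why the fix limits further covariates or penalises the model.

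Several stronger readings are tempting but unsupported:

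- **That the abstract and the Analysis section conflict.** They share dementia stage or severity, and two sets of examples can both be true. They are inconsistent in emphasis, no more.
- **That 25 events cannot support the listed covariates.** With no home or baseline effect, the Analysis section's list gave type I error 6.1% v 5.8% unadjusted and a median log odds ratio of 1.45 v 1.38 (true value 1.35), which is passable. Serious instability appeared only when both lists were combined, and nothing in the article plans that.
- **That baseline adjustment would save 15% to 25% of the variance.** That result is for continuous change scores with assumed correlations. The planned outcome is binary.

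**Conclusion.** The point holds in limited form. The randomisation is stratified by nursing home, the success test as described is not, and the two most relevant adjustment variables are not named for the regression. The planned test is valid and errs on the conservative side, and the sample size is right. The loss is about 1 point of power at a home SD of 0.5, 2 points at 1.0 and 4 points at 1.5, and nothing if homes do not differ.

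The power figures rest on equal-sized homes and an assumed between-home spread. The value of T0 Ashworth rests on the scale's ceiling, which the document gives, and on an assumed slope, which it does not. This is a worthwhile and nearly free improvement, not a flaw that undermines the conclusion.

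**What to change.** In the Analysis section:

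1. Test the difference in the proportion declined with a Mantel-Haenszel risk difference or a CMH test, stratified by nursing home and without continuity correction.
2. Include nursing home and a patient-level T0 Ashworth score in the logistic model. Four limbs are assessed, so build that score by the same rule that turns limb scores into the patient's declined or not-declined outcome.
3. Keep further covariates in that model few, or use penalised logistic regression, given about 25 expected declines.
4. Put fuller adjustment in a sensitivity analysis. Retain dementia type there, because the Bias section says that it is taken into account in the analysis.
5. Make the abstract's example covariates the same as those in the Analysis section.

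The cost is three degrees of freedom for home and one for T0 Ashworth, plus writing down the patient-level score. Randomisation already records home and the T0 assessment is already planned, so patients bear no extra burden.
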